#### Constipation severity

Constipation severity will be assessed by the Wexner constipation score, a validated and internationally adopted questionnaire for quantifying the severity of constipation [30]. The questionnaire consists of eight questions examining the clinical expressions of constipation, with scores ranging from 0 (best) to 30 (worst).

#### Fatigue

Fatigue will be assessed by the Dutch fatigue questionnaire (In Dutch: verkorte vermoeidheidsvragenlijst) [31]. The questionnaire consists of four questions on a 7-point Likert scale. Scores range from 4 (best) to 28 (worst).

#### Constipation specific (HR)QOL

Constipation specific (HR)QOL will be assessed by the Patient Assessment of Constipation-quality of life (PAC-QOL) questionnaire, a standardized and validated assessment of the burden of constipation on patients’ everyday functioning and well-being [32]. The PAC-QOL consists of 28 items on a 5-point Likert scale distributed over four subscales: physical discomfort, psychosocial discomfort, worries and concerns, and satisfaction. Scores within each subscale range from 0 (best) to 4 (worst). Subscale scores as well as a global score will be calculated, based on the mean of the included items.

#### Generic (HR)QOL

In adults, generic (HR)QOL will be assessed by the adult version of the EQ-5D-5L and the ICECAP-A questionnaires. The EQ-5D-5L comprises five dimensions: mobility, self-care, usual activities, pain/discomfort, and anxiety/depression. Each dimension has five levels: no problems, slight problems, moderate problems, severe problems, and extreme problems. The patients’ statements are combined into a 5-digit number that describes the patient’s health state [33]. EQ-5D utility scores will be derived using the Dutch value set for the EQ-5D-5L. The ICECAP-A is a measure of capability and consists of five attributes: stability, attachment, achievement, autonomy, and enjoyment [34]. Each attribute consists of one item with four response categories. Scores within each category range from 1 (worst) to 4 (best). As a Dutch valuation set is not yet available, the UK value set will be used to derive utility scores.

In adolescents, generic (HR)QOL will also be assessed by the adult version of the EQ-5D-5L. According to the EQ-5D guideline, in children aged 12 to 15 years, both the youth version and the adult version might be used. In children over 16, the adult version is recommended [35]. Additionally, the KIDSCREEN-27, a quality of life measure developed for children and adolescents, will be used as its items go beyond those measured in the EQ-5D [36]. The KIDSCREEN-27 is a widely used and psychometrically robust instrument suitable for clinical and epidemiological studies [36, 37]. It comprises five dimensions: physical well-being, psychological well-being, autonomy and parent relation, social support and peers, and school environment. Dimension scores will be transformed to Rasch person parameters, with higher scores representing better (HR)QOL [38].

#### Adverse events/complications

Adverse events and complications will be reported by the clinician in the case report form. Adverse events will be classified using the Clavien-Dindo classification of surgical complications [39, 40]. It will be described how often adverse events occur over time, in how many different patients, and in which treatment phase.

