### Sacral neuromodulation

Patients randomized in the SNM group will undergo a 4-week stimulation test period by a tined lead procedure (TLP). Detailed operative procedures for SNM have been described elsewhere [29]. The temporary quadripolar tined lead *(InterStim 3889 or 3093, Medtronic Inc., MN, USA)* will be connected to the external stimulator *(InterStim Verify 3531, Medtronic Inc., MN, USA)*. If successful, the quadripolar lead will be attached to an implantable pulse generator *(Interstim 3058, Medtronic Inc., MN, USA*). The operative procedures will be conducted under local or general anesthesia. Success of the TLP test period is defined as a DF ≥ 3 as measured by a 3-week defecation diary which is also used to assess eligibility for the RCT.

Patients with an implanted pulse generator have scheduled appointments at 4 weeks, 2, 3, 6, and 12 months. Patients will be asked to limit the use of additional conservative treatments for constipation such as laxatives and colonic irrigation. If patients use conservative treatment, they will be asked to document it.

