### Data collection and instruments

A 3-week defecation diary will be completed during the screening period/baseline (t0), 4-week follow-up (equal to the TLP test period in the SNM group) (t1), and at 3- (t2) and 6-month (t3) follow-up. Clinical and (HR)QOL secondary outcomes will be measured at the same time points. Resource use and costs will be assessed at t0, t2, and t3. In patients in the SNM group who still have the pacemaker at 12-month follow-up, the DF, constipation severity, generic (HR)QOL, and adverse events and complications will be assessed (t4).

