### Statistical analysis

All statistical analyses will be conducted according to the intention-to-treat principle using SPSS (SPSS, Inc., Chicago, IL, USA). Drop-outs will be classified as failures and missing values will be imputed using multiple imputation stochastic regression imputation. Values to impute will be drawn using predictive mean matching. *P* values of 0.05 and lower will be considered to indicate statistical significance. The number of patients with treatment success will be displayed by frequencies and percentages. Logistic regression, adjusted for the effect of possible unbalanced distributions of baseline characteristics, will be used to assess the difference in proportions of patients treated successfully at 6 months between the SNM and PCT group. Multivariable linear mixed-effect models corrected for covariates at baseline will be used to analyze differences in trends of the average DF a week between the SNM and the PCT group.

For the secondary outcome parameters, dichotomous parameters will be displayed using frequencies and percentages. Differences in proportions between the SNM and PCT group will be analyzed by means of logistic regressions, adjusted for the effect of possible unbalance of baseline characteristics. Continuous parameters will be presented as mean and standard deviation if distributed normally and as median and quartiles if not normally distributed, as judged using histograms. The difference in scores between the SNM and PCT group at 6 months will be analyzed by means of linear regression, adjusted for the effect of possible unbalanced distributions of baseline characteristics. No statistical analysis will be conducted on the adverse events and complications.

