Third, the comparator chosen in our design is PCT, in contrast to sham-stimulation in previous RCTs [20, 46, 48]. Sham-stimulation was found to be undesirable and infeasible for three reasons. First, as SNM is a surgical technique with a risk of complications and persistent scarring, we find it unethical to conduct sham-surgery with implantation of an expensive device. Second, for proper blinding of the patients, stimulation in the intervention group should be conducted at a subsensory level. However, as previously stated, subsensory stimulation is regarded suboptimal [52]. Third, sham-surgery would complicate the screening phase as this phase aims to discriminate between responders and non-responders. Only patients that show a clinically relevant improvement in the screening phase will receive permanent stimulation. It is expected that, during the screening phase, most patients in the sham group will not respond, as they are not receiving electrical stimulation. Hence, if a sham group would be included in this RCT, only the few patients that show a substantial placebo effect during the screening phase could be included in the permanent (sham-) stimulation phase.

Besides sham-surgery and sham-stimulation, comparing SNM to other surgical procedures such as colostomy or colectomy is also undesirable as these interventions are invasive and irreversible, and are associated with high morbidity and mortality rates [9, 13]. Moreover, patients show strong aversion towards these invasive interventions (data not published). Furthermore, as SNM might be a treatment step prior to colectomy or colostomy, it is clinically more valuable to compare SNM to conservative treatment instead of these surgical interventions.

In short, when comparing our study protocol to the already published RCTs, substantial differences can be found in terms of methodology and study population. The No.2-trial will assess the (cost-)effectiveness and budget impact of SNM compared to PCT. The results will contribute to the knowledge of using SNM in patients with slow-transit constipation and will support reimbursement decision-making in the Netherlands.

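### Adverse events by treatment phase need numbers and time at risk beside the counts, and the 12-month safety assessment should not be limited to patients who still have the device

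*Protocol article*

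**What the plan says.** All references are to the protocol article.

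- **Summary planned.** Under Adverse events/complications, "Adverse events and complications will be reported by the clinician in the case report form". Events are graded on a surgical complication scale, and "It will be described how often adverse events occur over time, in how many different patients, and in which treatment phase". No denominator or time at risk is named, and none is ruled out.
- **No further analysis.** Under Statistical analysis: "No statistical analysis will be conducted on the adverse events and complications". The description above is therefore the only adverse event summary the article states.
- **Phases in the SNM arm.** Under Sacral neuromodulation, every patient randomized to SNM starts with a 4-week test. After that, "If successful, the quadripolar lead will be attached to an implantable pulse generator". The Discussion confirms the restriction: "Only patients that show a clinically relevant improvement in the screening phase will receive permanent stimulation".
- **Assessment after month 6.** Data collection and instruments schedules one further assessment (t4), covering defecation frequency, constipation severity, generic quality of life, and adverse events and complications. It is specified for this group: "In patients in the SNM group who still have the pacemaker at 12-month follow-up". Footnote a to Fig. 1 has the same restriction.

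**The concern.** A description by phase invites the reader to compare phases, for instance to conclude that complications cluster in the test period or build up after implantation. Counts support such a comparison only if the phases have similar time at risk, and here they do not. The test phase is short and includes everyone. The implanted phase is several times longer and includes a selected subset.

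The t4 rule adds a separate problem. It makes assessment of safety after month 6 conditional on keeping the device until month 12. Explantation may itself be the result of a complication, so the rule can remove the events that a late safety summary is meant to show. The article does not say how events before explantation in these patients enter the months 6 to 12 period.

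Adverse events are a listed secondary outcome, complication costs are an SNM cost item in the economic evaluation, and the results are to inform a reimbursement decision. A late-phase picture drawn from device survivors would be less useful for that purpose.

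**Working it through.** The article states no adverse event figure to reproduce. The one design figure used is the SNM arm size: 64 × 3/5 = 38.4, stated as 38.

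**Inputs**
- SNM patients: 38 (Sample size calculation).
- Test phase: 4 weeks = 28/30.44 = 0.92 month (Sacral neuromodulation).
- Implanted phase to month 6: 6 − 0.92 = 5.08 months. Last period, months 6 to 12: 6 months. Assumption: time runs from the start of the test, and implantation follows it directly.
- Fraction implanted, f: not given. Assumed range 35% (the planned 6-month success rate) to 63% (the top of the success rates from non-randomized studies cited in the Background). Neither is presented as a test pass rate, so f = 100% is shown as the upper limit.
- Assumed for illustration: the same monthly event rate in all phases, and devices retained to month 12.

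**Patient-months at risk** = number at risk × phase length

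| Phase | f = 35% | f = 63% | f = 100% |
|---|---|---|---|
| Number implanted | 38 × 0.35 = 13.3 | 38 × 0.63 = 23.9 | 38 |
| Test | 38 × 0.92 = 35.0 | 35.0 | 35.0 |
| Implanted to month 6 (× 5.08) | 67.6 | 121.6 | 193.0 |
| Months 6 to 12 (× 6) | 79.8 | 143.6 | 228.0 |

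**Ratio of expected counts at an equal rate**, implanted phase to month 6 over test phase: 67.6/35.0 = 1.9; 121.6/35.0 = 3.5; 193.0/35.0 = 5.5. The ratio equals f × 5.08/0.92, so it exceeds 1 whenever f is above 0.92/5.08 = 18%.

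**Share of events by phase at an equal rate** (test / implanted to month 6 / months 6 to 12): 19% / 37% / 44% at f = 35%, and 8% / 42% / 50% at f = 100%.

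**Percentages of patients do not repair this alone.** At an assumed 0.05 events per patient-month, the expected share of at-risk patients with at least one event is:
- test: 1 − exp(−0.05 × 0.92) = 4.5%
- implanted to month 6: 1 − exp(−0.05 × 5.08) = 22.4%
- months 6 to 12: 1 − exp(−0.05 × 6) = 25.9%

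The rise is due entirely to phase length. Dividing events by patient-months returns 0.05 in every phase, for example 1.75/35.0 and 3.38/67.6 at f = 35%.

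**The 12-month rule.** The assessments up to 6 months are not conditional on the device. The only scheduled assessment after month 6 is t4, and it is conditional. A patient explanted at month 9 has been at risk with the device for 3 months of the last period. Under a literal reading, that patient contributes neither those 3 months nor any event in them, including one that led to explantation. If another record captures the event but the denominator is the t4 group, numerator and denominator do not match. The documents give no explantation rate, so this effect cannot be sized.

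**The case against.** The strongest objection is that this argues from silence. The planned wording is compatible with percentages or rates, and table-level denominators are commonly left to a full protocol or analysis plan, neither of which is shown. Reporting by phase already keeps test-period events apart from implanted-phase events. The phase lengths are published, and no inference is planned. This largely stands: missing denominators alone would be little more than omitted detail. It does not answer the t4 restriction, which is a written rule about who is assessed.

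It can also be said that nothing prevents a clinician from recording a complication or explantation when it occurs. That is true, and it is why the text supports only that such events can be lost from the last period, not that they will be.

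Four stronger readings are tempting and not supported:

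- **That the SNM pattern over time merely reflects the schedule.** True differences in event rate between phases would also shape it. The influences also oppose each other: longer phases raise later counts, while fewer patients at risk lower them.
- **That events will appear to decline because appointments thin out.** Appointments do become sparser (4 weeks, then 2, 3, 6 and 12 months), but the article does not limit recording to scheduled visits. Visit spacing is not a measure of ascertainment.
- **That patients who lose the device are mostly those with complications.** The article gives no reasons for explantation. It is a possibility only.
- **That the life-long model will be fed raw phase counts.** The model takes probabilities from several sources, and nothing says that unadjusted counts are among them.

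**Conclusion.** The point holds as a low-cost improvement, not as a demonstrated error. Two things are established from the text. The SNM phases differ in length and in patients at risk, so counts by phase are not comparable as they stand. And the 12-month adverse event assessment is restricted to patients who still have the device, so the months 6 to 12 picture can omit events in patients explanted in that interval.

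For size, equal monthly rates would give about 1.9 to 3.5 times the test-phase count in the implanted phase to month 6. This rests on an assumed 35% to 63% implanted, a constant rate and retained devices. At 100% implanted the factor is 5.5. The direction holds for any pass rate above about 18%. The effect of the 12-month restriction cannot be quantified from the article. Sample size and primary analysis are not touched.

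**What to change.** 1. **Adverse events/complications:** for each SNM phase (test, implanted to month 6, months 6 to 12), report the number at risk, the patient-months up to explantation or end of follow-up, and events per patient-month, beside the planned counts of events and patients.
2. **Data collection and instruments:** state that adverse events up to and including explantation are counted for every implanted patient, not only for those who still have the device at 12 months. Align footnote a of Fig. 1 with this.

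The cost is some extra tabulation. It needs implant, explant and event dates, which should already be in the case report form; that should be confirmed. A rate per patient-month averages over the phase and would blur a cluster of events just after surgery, so the counts should stay beside it.

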#### Resource use

Resource use will be assessed by health registries and a cost-questionnaire. This questionnaire includes questions on resource use in the past 3 months and includes parts of the PRODISQ for measurement of productivity losses [41].

### Data management

Data management procedures for the trial are developed and monitored by the CTCM. All baseline and follow-up data will be entered in the online MACRO electronic data capture (EDC) system. This system is compliant to the Good Clinical Practice guidelines. All patient data will be entered onto an electronic case report form (eCRF) programmed in MACRO EDC by the CTCM. The eCRF system will have full audit trail, data discrepancy functionality, database lock functionality, and supports real time data cleaning and reporting. Upon the completion of the trial, all study-related data and trial documents will be archived securely and retained for a minimum of 15 years at the participating sites.

### Sample size calculation

The sample size calculation is based on the proportion of patients with treatment success at 6-month follow-up (primary endpoint). An absolute difference in success rate of 30%, with success rates of 35 and 5% for SNM and PCT respectively, is considered clinically relevant. The sample size required to detect this difference with a two-sided Fisher’s exact test equals 64 patients in total (alpha 0.05, power of 80 and 5% drop-out rate). With a randomization ratio of 3:2, 38 patients will be randomized to SNM and 26 patients will be randomized to PCT.

### Statistical analysis

All statistical analyses will be conducted according to the intention-to-treat principle using SPSS (SPSS, Inc., Chicago, IL, USA). Drop-outs will be classified as failures and missing values will be imputed using multiple imputation stochastic regression imputation. Values to impute will be drawn using predictive mean matching. *P* values of 0.05 and lower will be considered to indicate statistical significance. The number of patients with treatment success will be displayed by frequencies and percentages. Logistic regression, adjusted for the effect of possible unbalanced distributions of baseline characteristics, will be used to assess the difference in proportions of patients treated successfully at 6 months between the SNM and PCT group. Multivariable linear mixed-effect models corrected for covariates at baseline will be used to analyze differences in trends of the average DF a week between the SNM and the PCT group.

For the secondary outcome parameters, dichotomous parameters will be displayed using frequencies and percentages. Differences in proportions between the SNM and PCT group will be analyzed by means of logistic regressions, adjusted for the effect of possible unbalance of baseline characteristics. Continuous parameters will be presented as mean and standard deviation if distributed normally and as median and quartiles if not normally distributed, as judged using histograms. The difference in scores between the SNM and PCT group at 6 months will be analyzed by means of linear regression, adjusted for the effect of possible unbalanced distributions of baseline characteristics. No statistical analysis will be conducted on the adverse events and complications.

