### Study population and recruitment

The study population consists of adolescents (14–17 years) and adults (18–80 years) with idiopathic slow-transit constipation refractory to conservative treatment. Patients will be referred to one of the participating centers by their (pediatric) gastroenterologist, surgeon, or general practitioner. The inclusion and exclusion criteria assessed during the screening visit are shown in Table 1. All patients will fill out a 3-week defecation diary to assess compliance to the Rome-IV criteria for idiopathic constipation. Patients will be asked to report defecation frequency, type of bowel stimulation (natural/laxatives/irrigation), presence of straining, sense of complete evacuation, sensation of anorectal obstruction, time spent on the toilet, impairment of daily activities, and presence of bloating and pain. Further diagnostic tests will include a defecography to exclude possible outlet obstruction and a colonic transit time measurement using radio-opaque markers to assess potentially delayed colonic transit time [28]. Eligibility will be confirmed during an outpatient appointment and patients will be informed regarding the study. If patients are willing to participate, written informed consent will be obtained during an outpatient appointment with the researcher.

**Table 1 Tab1:** Inclusion and exclusion criteria to assess patient eligibility

Inclusion criteria	Exclusion criteria
• An average DF of < 3 per week	• Diagnosed with obstructed outlet syndrome
• Meet at least 1 other criterion of the Rome-IV criteria* for functional constipation	• Diagnosed with irritable bowel syndrome
• Refractory to conservative treatment	• Congenital or organic bowel pathology
• Age between 14 and 80 years	• Rectal prolapse
• Diagnosed with slow-transit constipation	• Anatomical limitations preventing placement of an electrode
*Rome-IV criteria for FC [1]: In ≥ 25% of defecations:	• Skin and perineal disease with risk of infection
• Straining	• Previous large bowel/rectal surgery
• Lumpy or hard stools	• Stoma
• Sensation of incomplete evacuation	• Coexisting neurological disease
• Sensation of anorectal obstruction	• Significant psychological comorbidity
• Manual maneuvers to facilitate defecation	• Being/attempting to become pregnant during study follow-up

*DF* defecation frequency, *FC* functional constipation

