### Randomization

After written informed consent, patients will be randomized according to the principle of minimization in a 3:2 ratio to SNM or PCT, using the online randomization database ALEA (ALEA software, TenALEA consortium, Amsterdam, the Netherlands), programmed by the Clinical Trial Center Maastricht (CTCM). Potentially confounding factors that will be used for minimization are study site, age, and gender. As SNM, a surgical intervention, is compared to conservative (medical) treatment, blinding to treatment allocation of patients and medical staff is not possible.

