### Primary and secondary outcomes

The primary outcome is treatment success at 6 months. Treatment success is defined as an average defecation frequency (DF) of ≥ 3 a week, based on a 3-week defecation diary. Patients with an average DF of < 3 a week are considered not successfully treated.

Secondary outcomes are (1) the proportion of patients with a 50% reduction in the proportion of defecations with straining, (2) the proportion of patients with a 50% reduction in the proportion of defecations with a sense of incomplete evacuation, (3) constipation severity, (4) fatigue, (5) constipation specific (health-related) quality of life ((HR)QOL), (6) generic (HR)QOL, (7) adverse events and complications, (8) resource use and costs, (9) cost-effectiveness, and (10) budget impact.

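### The primary model takes its covariates from observed baseline imbalance, so the minimisation factors and baseline defecation frequency are not guaranteed to enter and the primary P value is not tied to one model

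*Protocol article*

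**What the plan says.** The Statistical analysis section of the protocol article gives the only statement of the primary model: "Logistic regression, adjusted for the effect of possible unbalanced distributions of baseline characteristics". It names no covariate, no definition of imbalance and no cut-off. The same principle is applied to the secondary outcomes, with logistic regression for binary ones and linear regression for continuous ones. The mixed model for the trend in DF is corrected for baseline covariates, also unnamed, and does not concern the primary success endpoint.

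The Randomization section says that "patients will be randomized according to the principle of minimization in a 3:2 ratio to SNM or PCT", and that "Potentially confounding factors that will be used for minimization are study site, age, and gender". These three factors are not carried into the Statistical analysis section.

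The endpoint is a dichotomised diary count: "Treatment success is defined as an average defecation frequency (DF) of ≥ 3 a week, based on a 3-week defecation diary". The same instrument is used before treatment: "A 3-week defecation diary will be completed during the screening period/baseline (t0"). Entry requires "An average DF of < 3 per week" (Table 1). Baseline DF is therefore available for every patient, but it is neither a minimisation factor nor a named covariate.

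**The concern.** Observed imbalance is a poor criterion for choosing covariates in a randomised comparison. The better criteria are whether a variable was used in allocation and whether it is expected to predict the outcome.

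The rule works against the design in two ways. Minimisation exists to balance site, age and gender, so a rule triggered by imbalance will usually pass over those three. And baseline DF, which is measured with the same diary as the endpoint and is a natural prognostic candidate, enters only if the arms happen to differ on it.

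Two things are at stake. The first is modest: if the omitted variables are prognostic, standard errors and P values are somewhat too large and precision is lost. The second is credibility. The trial is open-label, few successes are expected, and the result feeds a reimbursement decision. With imbalance undefined, several logistic models would all comply with the text, and each gives its own primary P value.

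**Working it through.** **1. The plan's own figure.** Inputs from Sample size calculation: "with success rates of 35 and 5% for SNM and PCT respectively, is considered clinically relevant"; "two-sided Fisher’s exact test equals 64 patients in total"; alpha 0.05, power 80%, drop-out 5%, arms 38 and 26. Exact enumeration of the two-sided Fisher test gives power 0.810 at 36/24 (N = 60). Then 60 / (1 − 0.05) = 63.2, rounded up to 64. The figure reproduces, and power at the full 38/26 is 0.845. Sample size is not at issue.

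**2. Events available.** 38 × 0.35 + 26 × 0.05 = 13.3 + 1.3 = 14.6 expected successes. A model with treatment, site (two recruiting centres are named), age, gender and baseline DF has 5 parameters besides the intercept: 14.6 / 5 = 2.9 events per parameter. The chance of no success among 26 PCT patients at 5% is 0.95^26 = 0.26. In that case the ordinary maximum-likelihood odds ratio is infinite.

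**3. How often an imbalance rule would change the model.** With k independent candidate variables and cut-off c, the chance that at least one is flagged is 1 − (1 − c)^k. The protocol gives neither k nor c, so only a range can be shown:
- k = 4, c = 0.05: 1 − 0.95^4 = 19%
- k = 10, c = 0.05: 1 − 0.95^10 = 40%
- k = 6, c = 0.10: 1 − 0.90^6 = 47%
- k = 10, c = 0.10: 1 − 0.90^10 = 65%

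**4. Type I error, illustrative.** Assumptions not in the protocol: 6 candidate variables, one of them prognostic with odds ratio 1.0, 2.7 or 4.5 per SD; imbalance flagged at p < 0.10; simple randomisation; no drop-out; likelihood-ratio test; 38/26; 1,500 runs per scenario (Monte Carlo error about 0.6 points). With 20% success in both arms:
- fixed adjustment for the prognostic variable: 0.055 to 0.061
- one imbalance rule fixed in advance: 0.059
- smallest P value among the unadjusted model, four imbalance cut-offs and the fixed model: 0.081 to 0.101

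**5. Power, illustrative.** Same assumptions, 35% v 5%:

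| Odds ratio per SD | Fixed adjustment | Imbalance-selected | Gap (points) |
|---|---|---|---|
| 1.0 | 0.903 | 0.897 | 0.5 |
| 2.7 | 0.931 | 0.895 | 3.7 |
| 4.5 | 0.949 | 0.913 | 3.6 |

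These levels use a likelihood-ratio test and should not be set against the exact Fisher power of 0.845; only the gaps are of interest.

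A second simulation fitted the whole proposed set with a Firth likelihood (38/26, 1,500 trials). It assumed a gamma distribution of true DF with shape 4 and mean 1.3 per week, Poisson diary counts, the other three covariates non-prognostic, and simple randomisation. Power was 88.3% unadjusted, 90.6% with baseline DF alone and 89.2% with all four covariates. The full set gains 89.2 − 88.3 = 0.9 points over no adjustment, which is about one Monte Carlo standard error of a single estimate (√(0.89 × 0.11 / 1500) = 0.8 points). With 20% success in both arms, fitting the full set by ordinary likelihood ratio gave 7.3% type I error, against 6.5% unadjusted.

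Neither simulation uses minimisation or gives site, age or gender any prognostic weight. The loss from omitting those factors is therefore argued from principle and not measured here.

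**The case against.** The strongest defence is that the sentence is a journal summary. It excludes no covariate, and naming covariates or defining imbalance is ordinarily left to the full protocol or the SAP, which are not shown. The missing list and cut-off are indeed no finding on that ground. What remains is that the article states a selection principle, and a SAP that followed it faithfully would still let the data choose the covariates.

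A reader might infer more than the documents support:
- *That the plan leaves out the minimisation factors and baseline DF.* It does not; any of them could enter if judged unbalanced. They are only not guaranteed.
- *That the rule inflates type I error.* A single rule fixed in advance gave 0.059, inside the range for fixed adjustment. The 0.081 to 0.101 requires taking the best of six analyses, which the plan does not propose. Omitting prognostic allocation factors makes the test conservative.
- *That baseline DF is the strongest predictor.* This is plausible, but the document does not show it, and the entry limit on DF narrows its range. Nor does the document show that site, age or gender is prognostic.
- *That a known share of trials would have the model changed by chance.* The share runs from 19% to 65% under the inputs tried, none of which is in the protocol.

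It is also fair to object that five parameters on about 15 events is a burden and that the measured gain is small. That objection shapes the remedy: the set must be short and the fit must cope with sparse data. It does not rescue imbalance as the criterion.

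**Conclusion.** The point holds in a limited form. The primary and secondary regressions choose covariates by baseline imbalance. That ties the model to the observed data, tends to pass over the factors used in allocation, and admits baseline DF only by chance.

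The cost in power is small: about 1 to 4 points if the covariates are prognostic and close to nothing if they are not. Those figures rest on assumed prognostic strength, and the lower end is within simulation error. No inflation of type I error follows from a rule fixed in advance. The more important weakness is that, with imbalance undefined and 14.6 successes expected in an open-label trial, the text does not commit the sponsor to one primary P value. The change is worth making because it removes that freedom at little cost.

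**What to change.** Replace the imbalance criterion in the Statistical analysis section with a covariate set fixed in advance and used whatever the observed balance:
- **Primary endpoint:** treatment, study site, age, gender and continuous baseline DF, fitted by penalised (Firth) logistic regression so that an estimate exists even if no PCT patient succeeds.
- **Secondary outcomes:** the same minimisation factors; for continuous outcomes, the baseline value of that outcome in place of baseline DF.
- **Sensitivity analysis:** the unadjusted two-sided Fisher test on which the trial was sized.
- **Exploratory only:** any model with covariates added because they look unbalanced.

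The cost is wording plus a penalised fit, for which the availability of a routine in the planned software should be confirmed. Site, age and gender are recorded for minimisation and baseline DF comes from the screening diary, so no new data are needed and N stays at 64. The downside is a slightly heavier model at about 3 events per parameter, which is why the set should stay this short.
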